## Introduction

Soil-transmitted helminths (STH) infection, also known as intestinal worm infection, is a very common condition but remains a neglected condition globally. There are three dominant STH: roundworm (Ascaris lumbricoides), whipworm (Trichuris trichiura) and hookworm (Ancylostoma duodenale and Necator americanus)(1,2). Hookworm is the main STH causing anaemia, contributing to approximately 4 million DALYs globally per year (3).  STH primarily affects the world’s deprived populations, causes significant health and socio-economic repercussions and constitutes an important public health problem in developing countries. The WHO estimates that STH affects more than 1.5 billion people worldwide(4). Globally, the prevalence of hookworm and *Ascaris lumbricoides* is estimated as 13.6% for both species, while the prevalence of *Trichuris trichiura* is estimated as 11.6% in sub-Saharan Africa (4).

Schistosomiasis is a chronic waterborne diseases caused by blood flukes of the genus Schistosoma. It affects approximately 240 million individuals in the tropical and subtropical areas, and is prevalent in more than 78 countries, with nearly 800 million people exposed to the risk of infection(5,6). Schistosomiasis is a major cause of morbidity and mortality in Africa, South America, the Caribbean, the Middle East and Asia(7).  *Schistosoma mansoni* causes intestinal schistosomiasis producing severe organ pathologies such as hepatosplenomegaly with periportal liver fibrosis and portal hypertension which progress from abdominal pain and bloody diarrhoea. Urogenital schistosomiasis caused by *Schistosoma haematobium* leads to haematuria, dysuria, hydronephrosis, female genital schistosomiasis and calcification of the bladder.

Preventive chemotherapy has been a backbone strategy to control STH and schistosomiasis, but for effectively controlling these NTDs, improved access to safe water, adequate sanitation, vector control, and health education is also needed and can accelerate progress towards elimination of these NTDs(8–10).

The WHO recommends benzimidazole drug (400mg albendazole or 500mg of mebendazole) against STHs, with pre-school-aged children (one to four years old) and school-aged children(five to 14 years old) living in the area where the prevalence of STH is over 20% targeted for annual or biannual treatment (11). For schistosomiasis, preventive chemotherapy with praziquantel is targeted at school-aged children, as they harbour the heaviest worm burden in a population. High-risk groups, such as fishermen and women who frequently visit contaminated water sources, are also targeted for mass treatment(12).

The WHO target is for at least 75% children to be covered through mass drug administration in areas at risk for STHs and schistosomiasis. Based on the WHO guidelines for evaluating STH and schistosomiasis at the community level(13), 9-10 years old school children should be the primary target population (i.e. Primary 4 and 5 students in the Ugandan education system)

The Uganda NTD Master plan (2017-2022), highlights the high burden of the diseases, particularly in poor communities with limited access to health care, and inadequate information and means of prevention and control measures. The plan further categorises NTDs into two groups; those amenable to preventive chemotherapy (PC-NTDs) and those controlled through case management (CM-NTDs). STHs and schistosomiasis are targets for preventive chemotherapy. Furthermore, the Uganda government was a signatory to the international treaties and conventions to eliminate targeted diseases and is committed to controlling and eliminating targeted NTDs by the year 2020. But, now, the WHO 2030 NTD roadmap suggests new global targets to prevent, control, eliminate, and eradicate a set of 20 NTDs. The WHO 2030 roadmap emphasises the necessity of shifting the roadmap from previous approaches to attain the goal of 2030: 1) Accelerating programmatic action within integrated platforms for delivery of intervention, 2) Cross-cutting approaches must replace the single disease elimination approach, 3) Country ownership is essential to sustain the achievement obtained through previous NTDs programs(14). The Ugandan government launched its national sustainable plan for NTDs in February 2021 as one of the first NTD endemic countries to announce a comprehensive NTD sustainability plan(15). In this plan, the Ugandan government emphasises:

1) Multi-sectoral collaboration.

2) Integrating NTD services within the broader health care delivery system.

3) Strengthening advocacy to increase the portion of domestic funding for NTD from 12% to 25% by 2025.

4) Identification indicators for monitoring the progress on NTD programs.

- - 1. **Mayuge NTDs Elimination (MANE) project**

World Vision, funded by Korea International Cooperation Agency (KOICA), has implemented comprehensive NTD elimination programs targeting STHs and schistosomiasis in Mayuge district since 2019, known as the Mayuge NTDs Elimination (MANE) project. The MANE project is a three-year program composed mainly of mass drug administration (MDA), water, sanitation and hygiene (WASH), and awareness increasing programs for the communities and health workers. For the WASH component, of 13 sub-counties of Mayuge district, two sub-counties covering 25,000 population will benefit from the piped water system. The MANE project has been constructing constructs nineteen public latrines in selected schools and implemented community-led total sanitation (CLTS) programs in 25 villages. For increasing awareness program, the MANE project has utilised a citizen voice and action (CVA) program developed by World Vision to improve people’s awareness of their public health issues and strengthen the relationship between the community and the authorities.

In 2019, a prevalence survey was done as the baseline survey to understand the burden of STH and schistosomiasis in Mayuge district. According to the WHO guideline, the MANE team selected the samples from 1,123 9-10 years old children who are equivalent to P4 and P5 grade students in the Ugandan education system (13). Baseline prevalence of schistosomiasis was 27.2% (305/1,123) and prevalence of STH was 15.8% (177/1,123). Among the 177 identified STHs positive samples, 96% (n=170) of STHs were hookworms.

- - 1. **Hookworm dominance in the prevalence of STH**

Mayuge district has implemented an annual MDA program against STHs targeting school-aged children since 2003. According to the MANE baseline survey of 1,123 children in the same age group in July 2019, the prevalence of hookworm was 15.1%, while the prevalence of Ascaris lumbricoides was 0% and prevalence of Trichuris trichiura was 0.6%. Thus, in Mayuge district, hookworm is the most common STH, and will be the focus of the current study. Considering the cure rate for hookworm by single-dose albendazole is thought to be 78.4%(16), and the high program coverage of MDA for STHs (77.2%, 81.4%, and 75% in 2012, 2014, and 2016, respectively), the continued burden of hookworm in Mayuge district suggests that hookworm has developed mechanisms to overcome the MDA campaigns.

- - 1. **Possible mechanisms for continued high prevalence of hookworm infection**

Proposed theories include the possibility that annual single-dose albendazole use for MDA is not enough to effectively treat hookworm; organisms have developed albendazole resistance traits; or that the effect of annual monotherapy with benzimidazole drugs has been handicapped by intrinsic environmental and social factors(17).

- - - 1. **Drug resistance in hookworm**

It has been demonstrated that overuse of benzimidazole drugs in animals is associated with the development of anthelmintic resistance, such as single nucleotide polymorphisms (SNPs) in the beta-tubulin isotype 1 gene at codons 167, 198 and 200 (18,19). In the same vein, benzimidazole has regularly been used to control STHs that may cause drug resistance against STHs in human(17). However, in hookworm-infected humans, benzimidazole drug resistance has not been reported yet(20,21). It appears more plausible that the current dose of albendazole targeting hookworm infection is inadequate to effectively control hookworm infection in humans due to reasons other than albendazole resistance.

- - - 1. **Infection intensity**

The cure rate of anthelminthic drugs against STH decreases when faecal egg count is high at pre-treatment (22). But, it is also known that the fecundity of residual female hookworm increases after treatment, caused by the relaxation of adult hookworm density(23,24). It means that the faecal egg count reduction test (FECRT) can reveal a wide range of drug efficacy against STHs within different human STHs cases. Kotze and Kopp suggested exclusion of cases with the heaviest infections from a FECRT to improve the interpretation of FECRT as an indicator of drug efficacy(24).

- - - 1. **Lack of absorbing albendazole and increasing albendazole absorption with fatty meal**

When it comes to albendazole absorption in the intestine, research has shown that albendazole absorption increases five to six-fold if taken with a fatty meal (25,26). Ceballo *et al*. assessed the serum pharmacokinetics of albendazole and its metabolites in eight Argentine adults. They showed a high variation of serum concentration of albendazole sulphoxide (ABZSX) among participants, which can be one reason why people show different cure rates when taking the same dose of albendazole (27). Therefore, it is necessary to consider and evaluate approaches for increasing albendazole absorption in order to improve drug efficacy against human hookworm, since individuals have different albendazole absorption.

In previous studies done in a range of countries; Brazil, Cameroon, Cambodia, China, Ethiopia, India, Lao PDR, Tanzania, and Vietnam, the cure rate of single-dose albendazole for hookworm ranged from 36 to 93%(22,28–30). According to the study done in Gabon by Adegnika *et al*., the cure rate of double-dose albendazole for hookworm was 92%; on the other hands, the cure rate of single-dose albendazole was 54% (31).

Avocado is one of the easily accessible foods containing high fat in rural areas of Uganda. 100 g of avocado contains 15g of fat, 2g of protein, and 8.5g of carbohydrate (32).

- - - 1. **Albendazole dissolution**

Albonico *et al* (2007)’s Nepal study investigated the efficacy of single albendazole manufactured in different pharmaceutical companies including the original manufacturer (GSK) and two other generic drugs targeting STHs(33). Dissolution time among the three tested drugs differed. The two generic drugs did not dissolve as well as the original drug made by GSK, which affected the cure rate of albendazole against hookworm. For hookworm, with albendazole made by GSK the cure rate was 74.3% compared to, with two other generic drugs, 53.3% and 50.7% respectively. Lower dissolution affects lower active doses for anthelminthic effect in gastrointestinal tract. Therefore, children must be informed to chew the chewable albendazole before swallowing to maximise drug efficacy against hookworm. Belew *et al* (2015)’s Ethiopia study also shows different cure rate between two albendazole brands against hookworm(34). One drug is more efficacious than the other drug with significant difference (*p*-value < 0.05) of egg reduction rate (98.1% versus 88.7%). The authors explained that low albendazole dissolution rate reduced bioavailability, which eventually lowered in-vivo drug efficacy against hookworm. They demonstrated that one brand of albendazole’s dissolution rate was four times higher than the other brand of albendazole used in the study.

- - - 1. **Sociocultural and environmental factors**

In addition, sociocultural and environmental factors affecting the high incidence rate of hookworm infection have been reported in multiple study populations (35–39)(40,41), which would be plausible reasons for hookworm reinfection among treated people. These factors require further investigation in Uganda.

| **Risk factors** | **Hookworm infection** | **Country** | **Reference** |
| --- | --- | --- | --- |
| Boys | OR=2.33 (95% CI=1.23-4.42, *p*-value:0.01) | Honduras | Gabrie *et al*. |
| Population density | OR=0.86 (95% CI=0.63-0.73, *p*-value:0.001) | Tanzania | Riess *et al*. |
| Temperature | Correlation with incidence of hookworm:  *r*_s_ = - 0.468 (p-value: 0.018) | Sri Lanka | Gunawardena *et al*. |
|  | Mean annual land surface temperature  *day: OR=0.81(95% CI=0.75-0.88, *p*-value:0.001)  *night: OR=154(95% CI=1.44-1.64, *p*-value:0.001) | Tanzania | Riess *et al*. |
| Barefoot | Incidence rate ratio(IRR)= 4.2 (95% CI= 1.2-14.5, *p*-value: 0.023) | Thailand | Jirannankul *et al*. |
|  |  |  |  |
| Raising animals | IRR=4.8 (95% CI=1.9-11.8, *p*-value : 0.001) – raising buffalos | Thailand | Jirannankul *et al*. |
| Water exposure |  | | |
| Wastewater farmers | OR=31.4 (95% CI=4.1-243, *p*-value: 0.001) compared to regular farmers on risk of nematode and hookworm infection | Pakistan | Ensink *et al*. |
| Bathing and washing with water from water fall | OR=2.33 (95% CI=1.35-4.01, *p*-value : 0.001) | Sri Lanka | Gunawardena *et al*. |
| The use of wells | OR=2.35 (95% CI=1.29-4.30, *p*-value : 0.005) | Sri Lanka | Gunawardena *et al*. |
| Lack of latrines | OR=1.60 (95% CI=1.01-2.53, *p*-value : 0.045) | Sri Lanka | Gunawardena *et al*. |
|  | OR=1.02(95% CI=1.01-1.04, *p*-value : 0.002) | Tanzania | Riess *et al*. |
|  | OR=1.90 | Kenya | Olsen *et al*. |
| School deworming(None or only once a year) | OR=10.57 (95% CI=4.53-24.66, *p*-value:0.001) | Honduras | Gabrie *et al*. |

(Table 1) Risk factors for hookworm infection

1. Aims and objectives

***Aims*:** After identifying the prevalence of STHs and schistosomiasis in Mayuge district to evaluate the impact of the MANE project on the burden of STHs and schistosomiasis, the study aims to assess the efficacy of albendazole with different doses and when co-administrated with fatty meals against hookworm, the dominant form of STHs in Mayuge district, Uganda. This study is designed to verify why hookworm is still prevalent regardless of more than fifteen years’ MDA program in Mayuge district and suggest an alternative MDA option for reducing hookworm prevalence. The evidence generated from this study will guide effective MDA option for STHs.

## 2.1 General objective

The general objective is to investigate approaches for improving the effectiveness of albendazole treatment for curing hookworm infection.

## 2.2 Specific objective

i. To determine the effect of albendazole administration with a fatty meal such as avocado, versus albendazole administration without a fatty meal, on hookworm cure rate and egg reduction rate.

ii. To determine the effectiveness of dual-dose (400mg/day, two consecutive days) versus single-dose (400mg) albendazole treatment regimens on hookworm cure rate and egg reduction rate.

iii. To identify and evaluate environmental, social and cultural variables affecting hookworm infection, and cure rate and egg reduction rate of albendazole against hookworm.

1. Methodology

This study will be embedded within the framework of the MANE project. The baseline prevalence survey was completed in July 2019, and the second prevalence survey is scheduled in September 2021 to evaluate the impact of programs implemented between 2019 and 2021.

## 3.1 Study area

Mayuge district is located in south-eastern Uganda and borders on Jinja, Iganga, Namayingo, and Bugiri. It is situated next to Lake Victoria. Mayuge is 146 km away from Uganda’s capital, Kampala. It has 13 sub-counties. According to the result of the registration activity in 2020, which was done as a part of the MANE project, Mayuge’s population is 509,118; with 95,418 children under five; and 156,182 children between five and 14 years old. It has a total of 504 primary schools, 41 health centres (HCs), and one hospital (HC II-34, HC III-5, HC IV-2). There are 1,536 health workers, and they work to raise awareness of MDA.

## 3.2 Study design, inclusion and exclusion criteria

The study will have two phases. The first phase will be a descriptive cross-sectional study which will evaluate the prevalence of STHs and schistosomiasis in Mayuge district as the follow-up survey of the MANE project.

In the second phase, children who have hookworm infection in this cross-sectional survey, will then take part in a randomised controlled trial with factorial design to assess impact of dual- vs single-dose albendazole and impact of taking albendazole with fatty foods on cure rate and egg reduction rate. Outcomes will be assessed at a follow-up visit 21 days after albendazole treatment.

In Mayuge district, primary four and primary five students will be the target population. Target schools will be selected and a given number of the sample from each selected school confirmed. Children whose parents/guardian signed consents for the children participating in the prevalence survey, and in the nested trial if hookworm infection is detected, will be included.

**Inclusion criteria are**

1. Children attending randomly selected primary 4 and 5 classes in one of the randomly selected schools and signed for child assent form
2. Children whose parents/guardian provide written informed consent for the prevalence survey and for the nested trial if hookworm infection is detected.

**Exclusion criteria are:**

1. Children who received praziquantel and albendazole within three months before the prevalence survey to avoid the residual effect of previously administrated drugs of praziquantel and albendazole.
2. Children who have a history of allergic reaction to either albendazole or praziquantel.
3. Children whose stool results come out as *Ascaris lubmricoides, Trichuris trichiura* ^[[1]](#footnote-1)^and other parasites infection apart from hookworm infection will not take part in the trial.

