## 3.4 Randomisation into four groups for the trial

When positive hookworm cases are identified through the prevalence survey, field workers will notify the students of "positive" results. These students will be requested to visit the school where they attend for participating in the trial. The field researchers will be formed by health personnel from the most accessible health centre IV or hospital-level health facility in Mayuge district: 1) Mayuge health centre IV located in Mayuge town council, 2) Kigandalo health centre IV located in Kigandalo sub-county, 3) Kityerera health centre IV located in Kityerera sub-county, and 4) Buluuba hospital in baitambogwe sub-county. The participants will be instructed to have a meal on the morning of the visit, following the protocol for taking fatty meal with albendazole as outlined in the study of Nagy *et al.*(25). These participants will be randomised into one group among four treatment options by applying the block randomisation method, stratified by health facility. The randomisation block size will be 8, and within each block there will be two participants allocated to each of the four trial arms. A randomisation list will be prepared beforehand using a random number generator. Each health facility will have its own random number list. The participants will take a meal four hours after the drug consumption to exclude the possibility of affecting albendazole absorption by immediate taking foods. But, water, no caffeine drinks, non-alcoholic beverages can be allowed during four hours fasting period.

Albendazole (AGOZOLE 400mg; batch number T11098, produced by AGOG Pharmaceutical Ltd., India) will be used for this trial. This is not a new drug. AGOZOLE albendazole is approved by the National Drug Authority (NDA) of Uganda and is widely available in the Ugandan domestic pharmaceutical market (NDA registered number: NDA/MAL/HDP/3013).

The trial is designed as an open-label randomised controlled trial with four arms:

Intervention group 1: participants will take 400mg of single-dose albendazole with 200 grams of avocado.

Intervention group 2: participants will take dual-dose albendazole without taking avocado. (Participants will take 400mg of single dose albendazole for two consecutive days)

Intervention group 3: participants will take dual-dose albendazole with 200 grams of avocado. (Participants will take 400mg of single dose albendazole with 200 grams of avocado for two consecutive days)

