Control group: participants will take 400mg of single-dose albendazole without taking avocado.

For participants in intervention groups 2 and 3, who are taking 400mg of albendazole on two consecutive days, they will be asked to return to the same clinic to do so.

If adverse events occur, the participants who have adverse events will be treated accordingly by the health workers who monitor the participants. If serious adverse events (SAEs) develop, these cases will be reported to VCD after recording the case(s) in the designated form, while managing the SAEs accordingly.

Three weeks after the treatment, the stool collection process will be repeated for those who participate in the treatment. These stool samples will be used to assess cure rate and egg reduction rate following albendazole treatment. If the MANE team find positive hookworm cases on the day 21 of follow up, the MANE team provide him/her alendazole again.

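### The allergy exclusion covers albendazole but not avocado, the other product the trial assigns, and does not say whether it applies to the survey or the trial

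*Protocol*

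**What the plan says.** Section 3.2 of the protocol gives one list of exclusion criteria for a two-phase study: a cross-sectional survey of soil-transmitted helminths and schistosomiasis, then a randomised factorial trial in the hookworm-positive children. The second exclusion is "Children who have a history of allergic reaction to either albendazole or praziquantel". The first, a three-month washout for praziquantel and albendazole, is tied to the survey. The third, infection with parasites other than hookworm, is tied expressly to the trial. The second is tied to neither.

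Section 3.4 sets out what the trial gives:

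- Reference arm: "Control group: participants will take 400mg of single-dose albendazole without taking avocado"
- Fatty food added: "Intervention group 1: participants will take 400mg of single-dose albendazole with 200 grams of avocado"
- Second dosing day added: "Intervention group 2: participants will take dual-dose albendazole without taking avocado"
- Both added: "Intervention group 3: participants will take dual-dose albendazole with 200 grams of avocado"

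For the last of these the protocol adds that "Participants will take 400mg of single dose albendazole with 200 grams of avocado for two consecutive days". Blocks are of eight, and "within each block there will be two participants allocated to each of the four trial arms". No arm contains praziquantel, and no criterion in the text shown mentions avocado or food allergy.

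**The concern.** The protocol accepts the principle that a history of reaction to a product should keep a child out. It applies this to albendazole but not to the other product it assigns. Avocado is no incidental detail: it is one of the two factors, the first specific objective, and one of the two comparisons on which the trial is powered. Yet the criterion names a drug that no trial arm contains.

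The main stake is safety. A child whose family already knows of a reaction to avocado meets every written criterion and can be allocated to eat it, on two days in one arm. A lesser stake is where the problem surfaces. Such a child needs special handling only if allocated to an avocado arm, so any refusal or non-adherence falls on one side of the avocado comparison. A check made before allocation would act equally on all four arms.

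The shared list raises a separate question of clarity. Read literally, the second exclusion also removes children from the stool and questionnaire survey, and the protocol gives no reason for that.

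**Working it through.** **Criterion against arms** (sections 3.2 and 3.4)

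| Product | Arms receiving it | Named in the allergy exclusion |
| --- | --- | --- |
| Albendazole | 4 of 4 | Yes |
| Avocado, 200 g | 2 of 4 | No |
| Praziquantel | 0 of 4 | Yes |

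The third exclusion removes children with other parasites from the trial, so praziquantel has no evident role for those randomised.

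**Share assigned avocado.** Each block of eight has two children per arm, and two arms include avocado: (2 + 2)/8 = 50%.

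- Section 3.6.1 total: 196/2 = 98 children.
- Fig 1 total: 4 × 53 = 212, and 212/2 = 106 children.

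The difference between the two totals is a separate matter and does not change the 50%.

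**The plan's own sample size, reproduced.** Inputs from section 3.6.1 are 70% versus 50%, 5% type I error (taken as two-sided) and 80% power. With the pooled-variance formula and mean proportion 0.6:

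n = [1.96 × √(2 × 0.6 × 0.4) + 0.8416 × √(0.7 × 0.3 + 0.5 × 0.5)]² / 0.20² = (1.358 + 0.571)² / 0.04 ≈ 93 per comparison group.

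The total is 2 × 93 = 186, and 186/0.95 = 195.8, so 196. Both agree with the protocol.

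**Children affected.** The documents give no rate of avocado reaction, so a range of 0.1% to 2% is assumed.

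| Assumed rate | Expected among 98 | Expected among 106 | Chance of at least one among 98 |
| --- | --- | --- | --- |
| 0.1% | 0.1 | 0.1 | 1 − 0.999^98 = 9% |
| 0.5% | 0.5 | 0.5 | 1 − 0.995^98 = 39% |
| 1% | 1.0 | 1.1 | 1 − 0.99^98 = 63% |
| 2% | 2.0 | 2.1 | 1 − 0.98^98 = 86% |

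**Effect on the avocado comparison if nothing changes.** If 2% of the avocado group went without it and gained none of its effect, a 20-point difference would become 20 × 0.98 = 19.6 points.

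**Cost of screening these children out.**

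- With replacement, 196/(1 − rate) rises to 197 at 0.1% and 200 at 2%.
- Without replacement, and after 5% loss, each comparison group has 98 × (1 − rate) × 0.95 children. That is 93.0 at 0.1% and 91.2 at 2%. Power is then 80.0% and 79.2%, against 80.0% as planned.

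**The case against.** The strongest reply is that the criterion does its main job. It excludes reaction to albendazole, which every child in the trial takes and whose dose is one of the two randomised factors. A reader might infer from the praziquantel wording and the missing avocado that the criterion protects nobody from what is being tested. The documents do not support that, because the study drug is covered.

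A reader might also infer that naming praziquantel is simply a mistake. That is not shown. The list is shared with a survey that includes schistosomiasis, and praziquantel also appears in the washout criterion tied to that survey, so the wording may be a survey or programme criterion. Nor can one say that survey children receive nothing: the protocol's footnote states that children positive for Ascaris or Trichuris will be treated with albendazole although excluded. This stands, and it is why the point is to state which phase the criterion serves and why, rather than to delete it throughout.

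A third tempting reading is that the gap materially biases or dilutes the avocado comparison. The arithmetic does not bear this out. Even at the assumed 2%, about two children are affected, against a loss allowance of 5% of 196, about 10.

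Finally, consent pages and one part of the protocol were not available to this review. Written parental consent and child assent are required, and a family told about the avocado might decline. That is fair, and it limits the finding to the criteria as shown. Consent is not an eligibility check, however, and the provision in section 3.4 for treating adverse events acts only after they occur.

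**Conclusion.** The point holds as a gap in eligibility wording. The trial's allergy exclusion covers albendazole and omits avocado, the other product assigned by randomisation. A child with a known avocado reaction is therefore eligible as the text stands, with a one-in-two chance of being assigned it. The list also leaves open which phase the exclusion applies to, and why praziquantel is named for a trial that does not give it.

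Half the randomised children are exposed to the gap. How many would be harmed or unable to comply cannot be taken from the documents: 0.1 to 2 of 98 rests wholly on the assumed 0.1% to 2%. No sample size, error rate or estimate in the plan changes to any extent that matters. The case rests on safety and coherence, and the priority is low.

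**What to change.** Reconcile the exclusion list in section 3.2 with the arm descriptions in section 3.4:

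- State for each exclusion whether it applies to the survey, the trial or both.
- Make the trial's allergy criterion consistent with every product the arms assign, including avocado.
- Check it in all hookworm-positive children before the allocation is opened, so that it acts alike on the four arms.
- Give the reason for naming praziquantel in the trial criterion, or remove it there. Whether it belongs in the survey criteria is for the sponsor to settle and state.

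The cost is an edited criterion and one question on the screening form. The downside is the loss of very few children: at most about four more to screen at the assumed 2% (200 rather than 196). The sample size calculation needs no change.
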